**Figure 4 figure4:**
[figure not shown]
Study timeline. aRMT: Active Remote Monitoring Technology; eCRF: electronic case report form; RADAR: Remote Assessment of Disease and Relapse.

### Progress to Date

The study started recruiting in the middle of June 2021. The data collection apparatus was setup and tested by clinical teams in April 24, 2021. All the questionnaires and their schedules are being served either via the RADAR active application or REDCap. Device selection (oximeter, spirometer, and wearable) was completed and the process of ordering devices was done before the start of recruitment. Garmin device (the choice of wearable in this study) integration has been completed, and the device has been tested with three dummy Garmin accounts for data sanity checks. All documentation required for the study was completed and was approved for funding and sponsorship. Patient and public involvement (PPI) feedback on the app and schedule was arranged with a demonstration of the app and protocol to participants. Relevant changes were incorporated based on PPI feedback. The ethics application was submitted and final approval was obtained prior to the start of recruitment. Eight participants have been recruited in the ILD arm of the study, and one participant has been recruited in the COPD arm. Looking at the data dashboard, it is evident that two exacerbations have already been captured. The real-time exacerbation detection system has been developed, and most of the parts of the infrastructure have been deployed and tested. The test data have been processed and are ready to feed into the algorithm. Currently, algorithm development is in progress, and we are using analyses from a priori data sets [13] and results from similar studies to inform the design of our algorithm.

## Discussion

### Conclusion

The RALPMH study was meticulously planned with collaboration from clinical teams, technical teams, and data analysis teams to provide a reference infrastructure for the use of wearable data for monitoring lung diseases. It specifically involves information regarding the feasibility and acceptability of remote monitoring and the potential of real-time remote data collection and analysis in the context of chronic lung disorders. Moreover, it provides a unique standpoint to look into the specifics of the novel coronavirus without burdensome interventions. It will help plan and inform decisions in future studies that make use of remote monitoring in the area of respiratory health.

### Ethical and Regulatory Considerations

#### Assessment and Management of Risk

Details on risk assessment are provided in Table 4.

**Table 4 table4:** Risk assessment.

Description of risk (indicate the level of likelihood: low/medium/high)	Risk priority (low, medium, high)	Risk owner	Proposed risk-mitigation measures
Data protection (eg, from intrusions)	Low	KCL^a^/SLAM^b^	Restrict access control to the data and use data sensitivity tiering. Encryption of data in transmission and at rest. Deidentification/pseudonymization once data are collected. Linked strong identifiers will be removed. Maintenance of software updates.
Threats to patient privacy	Low	KCL/SLAM	Data are handled with attention to deidentification and encryption. Higher risk data will typically be processed on edge devices with only aggregated data sent forward.
Patient fatigue with active or passive components of data collection	Medium	KCL/UCL^c^	Early engagement of acceptable burden levels to define expected tolerance levels. Opportunity to adapt the active data collection components in the course of the study.

^a^KCL: King’s College London.

^b^SLAM: South London and Maudsley NHS Foundation Trust.

^c^UCL: University College London.

#### PPI

This project was developed following discussions with patients and their families, who wanted to ensure that their lung disease could be safely monitored at home. Patients from IPF and COPD groups read a draft protocol in full, and their feedback was used to improve the final submitted protocol. Information for patients and the public will be posted on the Breathing Matters website [45], and the final results will be shared with the patients.

#### Protocol Compliance

A repeating form on REDCap will be used to log any contact with participants and document any deviations from the protocol. Notifications to the principal investigator or sponsor will be reported appropriately.

Significant deviation from the protocol or noncompliance may result in the removal of the participant from the study upon review.

Logged telephone contact will be made with participants throughout the course of follow-up if there is a loss of data stream from a device. The participant will be contacted by telephone to ensure compliance and correct use. These contacts will be recorded as evidence of feasibility and acceptability outcomes. In addition to the telephone call provided after the introductory training session, participants will receive a further call after 1 month to address any further concerns or questions.

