### Objectives

#### Primary Objective

The primary aim of the study is to evaluate cardiopulmonary disorders as potential targets for real-time, continuous, real-world remote monitoring. This study will investigate the potential benefit, acceptability, and feasibility of multiparametric remote monitoring of patient symptoms and physiology using commercially available wearable sensors for HR, activity, and SpO_2_; spirometry; phone sensors; questionnaires; and digital tests in patients with a range of pulmonary disorders.

The evaluation will be based on patient acceptability, dropout rates, and interpretation of data; detection of clinically important events, such as exacerbations and disease progression; quantification of symptoms (physical and mental health); impact of the disease on mood and well-being/QoL; and trajectory tracking of main outcome variables, symptom fluctuations, and order.

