### Outcomes

#### Acceptability of the Remote Monitoring System in the Three Disease Areas

The acceptability of the platform will be determined in terms of recruitment, retention, data completeness, and the qualitative experience of participants. The exit survey Technology Assessment Model Fast Form (TAM-FF) will also be used to evaluate the data collection infrastructure with participant feedback. The study will test both the feasibility and acceptability of tasks for participants. On completion of the data collection period, we will measure the total available data as a function of a theoretical maximum and assess data quality measured by a range of criteria, including missingness and contiguity.

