### Sample and Recruitment

#### Inclusion Criteria

The inclusion criteria are presented in Table 3.

**Table 3 table3:** Inclusion criteria.

Criteria	COPD^a^	ILD^b^	PH-COVID^c^
Clinical conditions	20 patients with a diagnosis of COPD	20 patients with a diagnosis of ILD	A clinical diagnosis of COVID-19 (within 4-13 weeks of enrollment) who report symptoms interfering with day-to-day activity present for more than 28 days following the onset of COVID-19
Gender	Male/Female	Male/Female	Male/Female
Age range (years)	18+	18-90	18+
Prior mobile phone use	Required	Required	Required
Willingness to use monitoring devices and complete study questionnaires	Required	Required	Required
History of exacerbation	2 or more exacerbations in the last 1 year	N/A^d^	N/A

^a^COPD: chronic obstructive pulmonary disease.

^b^ILD: interstitial lung disease.

^c^PH-COVID: posthospitalization COVID.

^d^N/A: not applicable.

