### Sampling

Convenient sampling will be employed for this pilot study.

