#### Sample Size

The study will include 20 participants for each of the three disease areas. This is a small sample feasibility study to assess the practical use of remote monitoring in three lung disease areas. The sample size will adequately allow objective assessment of the system deployed for this type of data collection in the typical patient population.

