#### Sampling Technique

Sequential participants who fit the inclusion/exclusion criteria will be identified from the respiratory outpatient clinics at the University College London Hospital (UCLH) and Royal Free Hospital (RFH).

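### Participants may be removed for noncompliance, which is itself part of the primary feasibility outcome, so the rule lets investigators act on the result

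*Protocol article*

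**What the plan says.** The Protocol Compliance section of the protocol article states: "Significant deviation from the protocol or noncompliance may result in the removal of the participant from the study upon review". The rule is discretionary. The article gives no threshold for it and does not say how a removed participant is counted afterwards.

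The Primary Objective section says: "The evaluation will be based on patient acceptability, dropout rates, and interpretation of data", followed by further items. The acceptability outcome is set out as: "The acceptability of the platform will be determined in terms of recruitment, retention, data completeness, and the qualitative experience of participants". The same outcome section plans to compare the data obtained with a theoretical maximum.

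The Data Analysis section adds descriptive statistics on attrition and on how many participants give adequate data. It also plans models for predictors of dropout and of the percentage of adequate data. Protocol Compliance itself says that telephone contacts prompted by a lost data stream will count as feasibility and acceptability evidence. Under Study Flow Chart, participants are asked about their experience when they exit as well as when they complete.

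On size: "The study will include 20 participants for each of the three disease areas".

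**The concern.** In most studies, removing a noncompliant participant affects who contributes to an outcome measured separately. Here compliance is a component of the outcome. A patient who stops wearing the device or answering questionnaires is a feasibility result, and the rule allows the study team to end that patient's participation because of it.

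Two things follow. Data after removal are never collected, so nobody can learn whether the patient would have re-engaged, for example after the support calls the protocol provides. The figures also change in a way that depends on bookkeeping. If removed participants leave the denominator, or their theoretical maximum is cut at removal, completeness is inflated. If they stay in, dropout no longer measures patient behaviour alone, and the planned dropout models would mix patient choices with investigator decisions.

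The results are meant to set the parameters of a larger study, so a distorted completeness or retention figure would carry over into its planning. Table 4 rates patient fatigue with data collection as a medium risk, so some noncompliance is expected.

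**Working it through.** The article states no completeness or retention target and gives no formula behind its sample size, so there is no figure to reproduce beyond 3 × 20 = 60 participants. The check asks how the removal rule moves the two outcomes under each way of counting.

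**Inputs.** From the article: n = 20 per cohort; 6 months of follow-up (stated for ILD/IPF, and as the upper limit for COPD). Assumed: k = 4 poor compliers (2 to 6 as a range), completeness of 80% in compliant and 20% in noncompliant participants, removal at month 2, and, for retention, 2 other participants who drop out voluntarily.

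**Completeness, k = 4**
- Nobody removed: (16 × 0.80 + 4 × 0.20)/20 = 13.6/20 = 68%.
- Removed participants excluded: (16 × 0.80)/16 = 80%.
- Maximum cut at removal: (16 × 0.80 × 6 + 4 × 0.20 × 2)/(16 × 6 + 4 × 2) = 78.4/104 = 75.4%.
- All enrolled, full 6-month maximum: (16 × 0.80 + 4 × 0.20 × 2/6)/20 = 13.07/20 = 65.3%.

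| k of 20 | Nobody removed | Removed excluded | Maximum cut at removal | All enrolled, full maximum |
|---|---|---|---|---|
| 2 | 74% | 80% | 77.9% | 72.7% |
| 4 | 68% | 80% | 75.4% | 65.3% |
| 6 | 62% | 80% | 72.5% | 58% |

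The last column falls below the first because removal stops data that would otherwise have arrived.

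**Retention, k = 4, 2 voluntary dropouts** (exact 95% intervals)
- Nobody removed: 18/20 = 90% (68 to 99).
- Removal counted as non-retention: 14/20 = 70% (46 to 88).
- Removed participants excluded: 14/16 = 87.5% (62 to 98).

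Excluding removed participants raises retention compared with counting them as failures, but not above the value seen when nobody is removed.

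**Recruitment.** Suppose 20 enrol from an assumed 25, 30 or 40 eligible patients approached, and 18 are retained. Uptake is 80%, 67% or 50%. Retention is 18/20 = 90% of those enrolled, but 18/25 = 72%, 18/30 = 60% or 18/40 = 45% of those approached. Reporting the number approached makes that gap visible.

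**The case against.** The strongest reply is that removal from the study is not removal from the analysis. The rule is permissive, and nowhere does the article exclude removed participants. Several provisions point the other way: dropout and attrition are reported, deviations are logged, contacts over lost data count as feasibility evidence, and experience is asked on exit. The denominator is also a detail that an article commonly leaves to the full protocol or analysis plan, and this is a descriptive pilot with no stated threshold for these figures to tip.

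Much of this stands. A reader might infer that the feasibility results will look better than they are. The text does not support that: with all enrolled kept in the denominator, the rule lowers both completeness and retention. The missing denominator is not itself the point. What remains is the rule as written. An analysis plan can fix a denominator, but it cannot recover data that were never collected or turn an investigator's decision back into a patient's.

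Three further inferences are also unsupported:
- A reader might see the entry criterion "Willingness to use monitoring devices and complete study questionnaires" as an error. Unwilling people cannot be enrolled in a consented monitoring study. The criterion limits generalisability, and its effect can be seen through the recruitment component.
- A reader might see a contradiction between "Convenient sampling will be employed for this pilot study" and "Sequential participants who fit the inclusion/exclusion criteria will be identified from the respiratory outpatient clinics". Taking successive eligible patients from accessible clinics is a common form of convenience sampling, and a log of those approached gives a denominator under either label.
- A reader might want people who fail the mobile phone criterion counted as non-acceptors. That criterion concerns prior phone use and is not a response to the system, so counting them would confuse ineligibility with refusal.

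**Conclusion.** The point holds for the removal rule. Applied as written, it lets investigators act on retention, dropout and completeness, which are components of the primary evaluation. In the illustration with four poor compliers out of 20, completeness reads 12 points too high if removed participants are excluded (80% against 68%), 7.4 points too high if their maximum is cut at removal (75.4%), and 2.7 points too low if all enrolled keep a full maximum (65.3%). Retention is 87.5% or 70% depending on the count, against 90% with nobody removed.

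These sizes rest on assumed compliance rates, timing of removal and number removed; the article gives none of them. The direction of the distortion is not fixed by the document. That the rule acts on the outcome does not depend on the assumptions.

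**What to change.** - In Protocol Compliance, delete noncompliance as a ground for removal. At minimum, count each such removal as non-retention and report it with its reason, separately from voluntary withdrawal. Deletion is preferable because it also preserves the later data.
- Compute retention and completeness on all enrolled participants, against a theoretical maximum fixed over planned follow-up. For COPD this runs to 6 months or the first exacerbation, as the cohort section already states.
- Apply the exit feedback already described under Study Flow Chart to anyone removed or withdrawn.
- Report the numbers approached and declining alongside the recruitment figure.

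The cost is a short wording change and a simple log of people approached. Recruitment had begun when the article was published, so the change would be an amendment. The downside is that the reported feasibility figures may be slightly less favourable.

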#### Access to the Final Study Data Set

The full data set for analysis will be limited to the immediate research groups and to members who must additionally hold current contracts with King’s College London or University College London. The data analysis will be conducted in the appropriate data safe havens and university compute infrastructure.

A secondary pseudonymized (removing any potential identifiers, such as raw location and audio data, will be restricted to the locked primary data set), postprocessed, and deidentified set of derived features (eg, activity, HR, and sleep features) may be published for reference, benchmarking, and review as part of academic literature generated from this project.

### Limitations

The size of the cohorts and the duration of the study might not be enough to get accurate and expected results, but this is typical for most pilot studies, as we intend to figure out the correct size and duration of the study required for expected results, which can be further used to plan future longitudinal studies. This can be partly mitigated by attempting to recruit people who are at high risk of exacerbation.

### Dissemination Policy

Analysis and access to the primary data set will remain on secure King’s College London/University College London infrastructure and will be jointly owned by the co-investigator groups and institutions. The secondary deidentified and pseudonymized data set may be published by the project partners as part of analysis and publication dissemination activity, and this may include the use of repositories, such as Synapse [46], with the intended time aim of 12 to 18 months after the conclusion of data collection. Partners may be notified of the published results on the project website [47].

## Appendix

Multimedia Appendix 1 Data analysis algorithms and models.

Multimedia Appendix 2 CONSORT-eHEALTH Checklist (V 1.6.1).

## Abbreviations

AE-IPF: acute exacerbations of idiopathic pulmonary fibrosis
aRMT: Active Remote Monitoring Technology
CCLTE: Centers for Disease Control and Prevention COVID-19 long-term effects
COPD: chronic obstructive pulmonary disease
eCRF: electronic case report form
ERS: Exacerbation Rating Scale
GAD-7: Generalized Anxiety Disorder scale
HR: heart rate
ILD: interstitial lung disease
IPF: idiopathic pulmonary fibrosis
mHealth: mobile health
NHS: National Health Service
PCFS: post-COVID functional status
PHQ-8: Patient Health Questionnaire depression scale
PIS: participant information sheet
PPI: patient and public involvement
QoL: quality of life
RADAR: Remote Assessment of Disease and Relapse
RADAR-CNS: Remote Assessment of Disease and Relapse – Central Nervous System
RALPMH: Remote Assessment of Lung Disease and Impact on Physical and Mental Health
RFH: Royal Free Hospital
RHR: resting heart rate
SpO_2_: oxygen saturation
UCLH: University College London Hospital
WHO: World Health Organization
